## Methods/Design

The following hypotheses will be tested by means of a RCT comparing the effects of UL action observation versus physical practice in improving the UL activity in children with HCP:

• If the MS works in terms of action goals, regardless of the kinematic properties, there will be a better improvement in the goal of UL use rather than in the kinematics of UL;

• OTI will be able to induce more changes in UL activity than those due only to the physical practice of the same actions;

• OTI will result in greater enhancement of daily activity performance;

• OTI will result in a greater mirror circuit re-organisation compared to action execution only and this cortical plasticity will be retained for longer periods.

These experimental hypotheses will address the following specific aims:

• OTI model is a novel training method where the main core is to observe an UL performing tailored goal actions, with the intent to imitate. This study will determine if this model is useful to enhance activity performance and, if there are improvements, for how long that effect will be retained;

• If OTI model will enhance the activity performance, new models of the rehabilitation setting in clinical practice will be proposed;

• If OTI model results in greater brain plasticity, the functioning of MS and its role in learning also in children with brain lesion will be demonstrated;

• If OTI model will be a good tool, it will guide practice also in other disabilities.

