### Brain Reorganization

Some of us [61] recently have performed a study using fMRI to explore the activation of human anterior intraparietal area (AIP) during the observation of complex object-manipulation tasks (e.g. inserting a key in a lock and turning it) as compared to simple tasks (e.g. whole hand grasping of an object) executed with the left and the right hand in a first person perspective. The results showed that, in general, both complex and simple tasks produced an activation of the fronto-parietal mirror system and that the activity of AIP in each hemisphere was higher during observation of the contralateral hand (hand identity effect). A Region-Of-Interest (ROI) analysis of the parietal activations responding to hand identity showed that each AIP was more active during the observation of complex with respect to simple tasks. In the right AIP this effect was stronger during observation of the contralateral hand, in the left AIP was stronger during observation of both hands. This complexity related property was not observed in the other activated areas. These findings support the concept that the observation of motor acts retrieves the internal representation of those same acts in the observer's motor system (direct-matching hypothesis based on the mirror neuron mechanism). This study was conducted in adults, but our group have large experience in performing fMRI with children [62-67]. To obtain a better compliance by the children the paradigm used with the adults was reduced in the time of acquisition and only two functional series (see later) will be acquired.

The main aims of this part of the study will be:

• to explore the MS in children with HCP and

• to provide, if there are, some evidences of plastic changes after action-observation training either on the MS or in the somatosensory cortex.

To verify the first hypothesis, a group of healthy age-matched children will be enrolled. For the second hypothesis, a subgroup of children with HCP recruited for the study and randomised to the experimental or control group (see inclusion criteria) will perform fMRI before (T0) and after the training (T1 and T2) (see Figure 1).

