
#### - fMRI: Image acquisition, processing and analysis

Blood oxygen level dependent (BOLD) responses will be acquired by a 1.5 T MR system (General Electric Signa Horizon LX Milwaukee, USA), equipped with echo-speed gradient coil and amplifier hardware. Activation images will be acquired using Echo Planar Imaging (EPI) gradient-recalled echo sequence (TR/TE/flip angle = 3000 ms/50 ms/90°, FOV = 240 × 240 mm, matrix = 64 × 64, 5 mm thick slices). For MS exploration, time-course series of 132 scans for each volume will be collected in 16 blocks alternating between control and action conditions, resulting in an acquisition time for each series of 6'36'', repeated 2 times. For motor-sensory tasks, time curse series of 100 scans for each hand will be collected in 16 blocks alternating between Motor and Sensory conditions (each followed by a period of Rest), resulting in an acquisition time for each series of 5'00''. Each first block of each series included 4 initial extra scans to allow the stabilization of signal and this period will be eliminated from subsequent analysis. A volumetric set of data (3D FSPGR: TR/TE/TI/flip angle = 21.1 ms/3.8 ms/700 ms/10°; FOV = 280 × 280 mm, matrix = 256 × 256) will be also acquired to generate a 3D whole brain reconstruction. Data analysis will be performed using the Brain Voyager QX software package (Brain Innovation, Maastricht, the Netherlands). Before statistical analysis, raw data will be corrected for head movements and high-temporal filtered in order to exclude temporal drifts. For each subject, all the two-dimensional functional data will be co-registered, concatenated, aligned to the three-dimensional high-resolution images and finally transformed into Talairach space [68]. A General Linear Model (GLM) approach will be used to generate statistical parametric maps, using a hemodynamic response function modelled on the standard Boynton's function [69] and considering the four conditions: SR, SL, CR, CL. Moreover, because the side of HCP in the children enrolled could be right or left, to correct this effect, we will treat the processing delivered by the dominant hand as the unimpaired hand and whose by the non dominant hand as the impaired hand. A ROI analysis will be conducted on the statistically significant clusters coming out from the application of the GLM analysis. In these ROIs, a single-subject analysis will be also performed measuring the average per cent signal change of each individual subject.

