To test our experimental hypotheses we plan these main analyses, as follows:

• to investigate whether the used stimuli is able to activate the MS in children with HCP, we will contrast activity for all the observed actions vs the static conditions (hand action observation, all stimuli > static conditions) and if the activity in children with HCP will be different with respect to normal functional response (healthy children);

• to explore whether there are areas differentially responding to the identity of the observed hand, we will compare the activity related to observation of the simple and complex tasks performed by the corresponding impaired (non-dominant) hand with those performed by the unimpaired (dominant) hand;

• to study whether there are some changes after UP-CAT, a group analysis of intra-participant change in activation will be undertaken using a ROI approach both for MS and for the sensory-motor task.

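### The fMRI analyses listed to test the hypotheses cover change within children but no comparison of the arms, and the only stated correction for side of hemiplegia is relabelling the hands

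*Protocol article*

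**What the plan says.** The fourth hypothesis in the protocol article (Methods/Design) compares the arms: "OTI will result in a greater mirror circuit re-organisation compared to action execution only and this cortical plasticity will be retained for longer periods". Under Brain Reorganization, a subgroup from both randomised arms is scanned at T0, T1 and T2. The size of the subgroup is not given.

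The section on fMRI image acquisition, processing and analysis introduces its list with "To test our experimental hypotheses we plan these main analyses, as follows". Three analyses follow:

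- observed actions against static frames, with children with hemiplegia also compared with healthy children;
- observation of the impaired hand against the unimpaired hand;
- to look for change following UP-CAT: "a group analysis of intra-participant change in activation will be undertaken using a ROI approach", applied to the mirror-system and sensory-motor tasks.

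The Analyses section does plan a between-group comparison of change from baseline, but it opens by limiting itself to clinical data.

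On side of hemiplegia, the fMRI section notes that it may be right or left and gives one correction: "we will treat the processing delivered by the dominant hand as the unimpaired hand", with the non-dominant hand treated as impaired. Images are transformed to Talairach space. The article neither mentions nor rules out left-right realignment of the images.

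**The concern.** A claim of more reorganisation than with practice alone needs a contrast between the arms. Under Study treatment, control children carry out the same exercises in the same order, and the scanning schedule is common to both arms. Change within children therefore mixes the effect of observation with practice and with familiarity with the scanner. If the listed analysis is followed literally, significant change after training could be reported as evidence for the mirror-system hypothesis when it shows nothing specific to observation. The same risk arises if the arms are tested separately and the p values compared informally.

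The correction for side raises a second, smaller question. The adult study described under Brain Reorganization found that AIP in each hemisphere responds more to the hand on the opposite side. Relabelling hands without realigning hemispheres would set children with right and left hemiplegia against each other in a fixed-side ROI.

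**Working it through.** **Plan's own figure.** The article gives no sample size, effect size or power for fMRI. Its 12 per group is for AHA and does reproduce: 2 × (1.960 + 0.842)² / 1.16² = 11.7, rounded up to 12. It is used below only as the largest possible fMRI subgroup per arm.

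**1. What each analysis estimates.** Let O be the effect of observation, P of practice and S of repeat scanning, assumed additive.

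- Change in the experimental arm: O + P + S
- Change in the control arm: P + S
- Change pooled over two equal arms: O/2 + P + S
- Difference between arms in change: O

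Only the last isolates the quantity in the hypothesis, and it is the one not listed.

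**2. Size of the problem.** Assumptions: O = 0, both arms change by a within-child d of 0.8, two-sided 5% t tests, n per arm from 4 to 12. Let w be the power of the test within one arm. The chance that the experimental arm is significant and the control arm is not is w(1 - w). For example, at n = 8 this is 0.496 × 0.504 = 0.25. The last two columns describe the missing between-arm test. They give its power at an assumed d of 1.16 (borrowed from the AHA calculation) and the d it detects with 80% power.

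| n per arm | w | Experimental arm alone significant | Pooled change significant | Arm contrast: power at d = 1.16 | Arm contrast: d at 80% power |
|---|---|---|---|---|---|
| 4 | 0.206 | 16% | 50% | 28% | 2.38 |
| 6 | 0.356 | 23% | 71% | 44% | 1.80 |
| 8 | 0.496 | 25% | 85% | 58% | 1.51 |
| 10 | 0.616 | 24% | 92% | 69% | 1.32 |
| 12 | 0.714 | 20% | 96% | 78% | 1.20 |

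With no true difference between arms, a direct arm contrast would be falsely significant 5% of the time.

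**3. Hand-identity contrast, if hemispheres are not realigned.** Let D be the excess response of AIP to the contralateral hand, equal in all children, and p the share with right hemiplegia. In left AIP, impaired minus unimpaired is +D in right hemiplegia, where the impaired hand is contralateral, and -D in left hemiplegia. The mean is pD - (1 - p)D = (2p - 1)D:

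- p = 0.5: 0
- p = 0.6: 0.2D
- p = 0.7: 0.4D

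Right AIP shows the same size with opposite sign. With the original right and left labels, right minus left in left AIP would be +D in every child, so relabelling on its own is what introduces the cancellation.

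**4. Change analysis, if hemispheres are not realigned.** Suppose training changes only the hemisphere with the lesion, and a share q of children have the lesion on the side of the ROI. The mean effect falls to q × 1.16. Adding the extra between-child variance in full gives 1.16q / √(1 + q(1 - q) × 1.16²).

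- q = 0.5: 0.58, or 0.50 with the extra variance
- q = 0.6: 0.70, or 0.61
- q = 0.75: 0.87, or 0.78

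This is dilution. An arm comparison remains possible.

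**The case against.** The strongest reply is that this is a condensed article and the arm contrast is unnamed but not excluded. Both arms are scanned, the planned group analysis is loosely worded, and UP-CAT is also the name of the whole study in the flow-chart caption, so changes after UP-CAT need not mean the experimental arm alone. Change per child is also exactly the quantity that an arm comparison would use. All of this is fair, and it rules out one inference a reader might draw: that the trial design cannot test the hypothesis. The design can, since the data will exist. What stands is that the article offers this list as the main analyses for its hypotheses, specifies the change analysis as within-participant, and names a between-group comparison of change only for clinical data.

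A reader might also infer that images from children with right and left hemiplegia are pooled unflipped. The article does not say so. Realignment may be in the full protocol, and the planned single-subject ROI measurements would allow labelling child by child. The (2p - 1)D result is therefore conditional. Full cancellation also needs p = 0.5 and an equal D in all children, and the effect itself comes from adults. It bears on the exploratory hand-identity contrast, not on the reorganisation test.

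A third tempting inference is that estimates are inflated because "A ROI analysis will be conducted on the statistically significant clusters coming out from the application of the GLM analysis" and signal change is then measured in those ROIs. That follows only if the selecting contrast and the tested contrast depend on each other, and the article does not say which contrast selects.

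Finally, fMRI is neither the primary nor a listed secondary outcome, and it is confined to a subgroup. Maturation is a weak rival explanation, given 15 treatment days and an 8-week follow-up. Practice and repeat scanning remain serious ones.

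**Conclusion.** The point holds for the analysis as written. The hypothesis is comparative, the listed change analysis is not, and nothing elsewhere in the article clearly supplies the missing contrast for fMRI. Under the assumed equal change in both arms, the uncontrolled readings would suggest an effect in 16% to 25% of trials (experimental arm significant, control arm not) or 50% to 96% (pooled change). These figures rest on an assumed d of 0.8 and assumed subgroup sizes. The conclusion itself needs only that practice and scanning are common to both arms.

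The correction for side is a secondary point. Taken alone it would partly or fully cancel the hand-identity effect in a fixed-side ROI, and it may dilute side-specific change, but it does not itself block the arm comparison. The AHA conclusion is not affected.

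**What to change.** State that the fMRI test of reorganisation is the between-arm difference in T1-T0 and T2-T0 percent signal change in the ROIs, for the mirror-system task and the sensory-motor task. Keep within-child change as description. Report the estimate with a confidence interval and give the subgroup size: with 4 to 12 per arm, only differences of about d = 2.38 down to 1.20 are detectable with 80% power. Because scanning ends at T2, limit the claim of longer retention to 8 weeks after treatment.

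Label each ROI as contralateral or ipsilateral to the impaired hand in each child, or state that one side's images are mirror-flipped. Flipping assumes rough left-right symmetry; labelling leaves the images untouched.

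While editing, name the contrast that defines the ROIs. T0 scans alone should not be called independent of T1-T0 change, because T0 is one of its terms.

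The cost is analysis wording and a processing step. No extra scans or children are needed.

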### Analyses

Clinical Data will be managed and analysed using the Statistical Package for Social Sciences (SPSS version 16.0). Descriptive statistics (means, standard deviation) will be calculated to summarise the data set for both groups and to identify potential baseline differences between the groups; p values will be used to indicate the strength of the evidence, a significant level of 0.05 will be used. Initially between group differences will be evaluated at baseline (T0) assessment point using Mann-Whitney U independent sample test for all Outcome Measure chosen. Within group changes between baseline and follow-up assessment (T1 and T2) will be evaluated using Wilcoxon matched-pairs sign rank test. A second level analysis with independent sample t test of the differences between the follow-up assessment and baseline (T1 vs T0 and T2 vs T0) will be performed for the comparison of the rehabilitative gain between the two groups. Moreover, Cohen's d values and their 95% confidence interval will be calculated to obtain a pre-post intervention effect size [70]. According to Cohen's work values of effect size below 0.2 will be considered to reflect "no effect", values from 0.2 to 0.5 a "small effect", values between 0.5 and 0.8 a "medium-sized effect", and values > 0.8 "large effect".

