**Methods/Design:**

The trial is designed according to CONSORT Statement. It is a randomised, evaluator-blinded, match-pair group trial. Children with HCP will be randomised within pairs to either experimental or control group. The experimental group will perform an Action-Observation Therapy, called UP-CAT (Upper Limb-Children Action-Observation Training) in which they will watch video sequences showing goal-directed actions, chosen according to children UL functional level, combined with motor training with their hemiplegic UL. The control group will perform the same tailored actions after watching computer games. A careful revision of psychometric properties of UL outcome measures for children with hemiplegia was performed. Assisting Hand Assessment was chosen as primary measure and, based on its calculation power, a sample size of 12 matched pairs was established. Moreover, Melbourne and ABILHAND-Kids were included as secondary measures. The time line of assessments will be T0 (in the week preceding the onset of the treatment), T1 and T2 (in the week after the end of the treatment and 8 weeks later, respectively). A further assessment will be performed at T3 (24 weeks after T1), to evaluate the retention of effects. In a subgroup of children enrolled in both groups functional Magnetic Resonance Imaging, exploring the mirror system and sensory-motor function, will be performed at T0, T1 and T2.

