### Study design

A matched pairs randomised, evaluator-blinded trial will be carried out using an action-observation intensive training program to evaluate the efficacy of OTI compared to physical practice only in children with HCP aged 5 to 15 years. Assessment will be performed at baseline (T0, on the week preceding the onset of the treatment), and then on the week (T1) and 8 weeks (T2) after the end of the treatment. A further assessment will be performed at 24 weeks (T3) after the end of the treatment to evaluate the retention of effects.

The experimental design and outcome measures are depicted in Figure 1.

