### Randomisation

After enrolment, children will be block randomised into pairs according to their activity level at House Functional Classification System [36,37] (grade 6-8 vs 4 or 5) using a computer generated set of random numbers. A computer random allocation will also be used to randomly assign the subjects of each pair to experimental or control group by a computer random allocation. We choose a matched pairs design because it minimises the likelihood of group differences at baseline that has often been present in UL rehabilitation studies [39]. All randomisation, sequence generation, and preparation of group allocation materials will be performed by a third party, who has no direct contact with the clinical aspects of the trial. The master list of random numbers will be located in locked cabinets only accessible at completion of the RCT for analysis.

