### Therapy protocols

The group of physical therapists and child neurologists planned 15 sets of daily life UL exercises. Each set is composed by three sequential UL goal actions of increasing complexity. The first 8 sets are unimanual exercises (total of 24), while the last 7 sets bimanual (total of 21) where the two upper limbs have different roles in an integrated action. In order to grade the activities with the range of children capabilities two series of sets were conceived, one for children grade from 6 to 8 at House Functional Classification System [36,37] and one for those grade 4 or 5. The setting of all exercises is the same but the proposed type of movement (i.e. range of movement) is simplified for the children with more severe impairment (grade 4 or 5). Each action of the two series performed by an actor was videotaped so that the videos showed only the hand and arm and in the first perspective; then each of this videos was edited so that each lasted 3 minutes. The actor used one or two hands respectively for the unimanual and bimanual exercises; collected videos were also tipped over, in order to have the same videos for the right and for the left hand. Moreover, 15 sets of computer games with no biological movements were chosen (i.e. quiz games, crossword, Simons etc.).

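### Arms are randomised within pairs formed on House band, but gains are compared with an independent-samples t test that ignores pair and band, so possible precision is lost

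*Protocol article*

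**What the plan says.** The Abstract and the Study design section both describe a matched-pairs trial: "Children with HCP will be randomised within pairs to either experimental or control group" and "A matched pairs randomised, evaluator-blinded trial will be carried out".

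The Randomisation section says how pairs arise: "children will be block randomised into pairs according to their activity level at House Functional Classification System", in two bands, 6-8 and 4 or 5. It names no other matching factor. Allocation is then made inside the pair: "A computer random allocation will also be used to randomly assign the subjects of each pair to experimental or control group". The reason given is balance, not precision: "We choose a matched pairs design because it minimises the likelihood of group differences at baseline".

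The Analyses section compares the arms by "A second level analysis with independent sample t test of the differences between the follow-up assessment and baseline", for T1 against T0 and for T2 against T0. The same section does name a matched-pairs test, but for another purpose: "Within group changes between baseline and follow-up assessment (T1 and T2) will be evaluated using Wilcoxon matched-pairs sign rank test". That pairs each child with himself or herself over time, not with the other member of the randomised pair. The article states no paired, pair-adjusted or band-adjusted comparison of the arms.

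**The concern.** When both members of a pair come from the same House band, the arms hold equal numbers from each band. Any difference between bands in average gain then cancels from the difference between arms. An independent-samples t test does not know this and leaves the between-band variation in its error term. If the bands gain differently, the standard error is larger than the design warrants, the p value is too large and the confidence interval too wide.

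With 24 children there is little precision to spare. The question is how large the loss could be, and whether adjusting carries any risk.

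**Working it through.** **Inputs from the article.** Effect size 1.16, significance level 0.05, power 80%, 12 per group (Sample size); 12 matched pairs (Abstract); two House bands (Randomisation).

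**Assumptions, not in the article.** Two-sided test, normal change scores with equal SDs, no dropout, half the pairs in each band, pairs formed at random within band. The effect of 1.16 is in units of the total within-arm SD of change. The gap *g* between band means of change, in within-band SDs, is unknown and is varied.

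**Step 1: the plan's own figure.** For two independent means, n = 2(1.960 + 0.842)² / 1.16² = 11.67, rounded up to 12 per group. So 12 follows from the independent-groups normal formula (power 81.1% at 12). With the exact noncentral t distribution, the independent test has 77.5% power at 12 per group and 81.0% at 13. The sample size and the stated test therefore agree with each other, and neither uses the pairing.

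**Step 2: from band gap to within-pair correlation.** With equal bands, the correlation of change within pairs is the share of variance lying between bands: ρ = (g²/4) / (1 + g²/4).
- g = 0: ρ = 0
- g = 0.5: ρ = 0.0625/1.0625 = 0.06
- g = 1: ρ = 0.25/1.25 = 0.20

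A variance share cannot be negative, so under this pairing the error can only be on the conservative side.

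**Step 3: excess standard error.** The independent-test standard error is too large by 1/√(1 − ρ) = √(1 + g²/4): 1.00, 1.03 and 1.12 for the three gaps.

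**Step 4: size and power.** The independent and band-adjusted columns were simulated. The paired column is from the noncentral t distribution.

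| Gap g | Independent t (22 df): true size | Independent t: power | Arm + House band (21 df): power | Paired t (11 df): power |
|---|---|---|---|---|
| 0 | 5.0% | 77.5% | 77.4% | 73.5% |
| 0.5 | 4.4% | 78.2% | 79.9% | 76.0% |
| 1 | 2.9% | 79.4% | 85.9% | 82.4% |

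The band-adjusted model keeps its size at about 5% throughout. As a check, its power from the noncentral t distribution, with noncentrality 1.16 × √(1 + g²/4) × √6, is 77.3%, 79.8% and 85.7%, within 0.2 points of the simulation. A split of 4 and 8 pairs between the bands gives nearly the same results.

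**Step 5: when a paired t test pays.** The critical values are 2.074 on 22 df and 2.201 on 11 df. The paired interval is narrower than the independent one only if ρ > 1 − (2.074/2.201)² = 0.11. Below that, the lost degrees of freedom outweigh the gain.

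**The case against.** The best defence is that nothing in the article shows the loss to be material. Matching is on two broad bands only, and change scores already remove each child's baseline level, so the within-pair correlation of change may be small. A correlation of 0.2 needs band means a full within-band SD apart in gain. At half an SD the adjusted model gains only about 2 points of power. With complete pairs, the difference in mean change is the same estimate under either analysis. All of this stands.

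Two stronger readings are tempting, and the article supports neither.

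- A reader might infer that the standard error is too wide as a matter of fact, because the bands train on different material ("two series of sets were conceived, one for children grade from 6 to 8 at House Functional Classification System"). The Therapy protocols section also says that the exercise setting is common to both series and that movements are simplified for grades 4 and 5. Tailoring of that kind could as easily make gains more alike. It does not establish a gap.
- A reader might infer that the benefit of pairing is thrown away. The only benefit the article claims is balance at baseline, which holds whatever test is used. No gain in precision was promised or built into the sample size.

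The objection does not remove the mismatch. The article names a specific test, the test leaves out the factor used in randomisation, and nothing else in the text makes up for it.

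**Conclusion.** The stated between-arm test does not follow the stated randomisation. It is valid in the sense that matters most: it does not raise the false-positive rate. It is conservative by an amount that depends on an unstated difference in AHA gain between House bands. Under the assumptions above, the power forgone is nil with no gap (the adjusted model is then 0.1 points lower), 1.7 points at 0.5 SD and 6.5 points at 1 SD.

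The gap is an assumption at every value, so these figures show a range and are not a forecast. The change should be made because it gives up almost nothing if the bands do not differ and recovers precision if they do. It is an improvement in efficiency, not a correction on which the trial's validity depends.

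**What to change.** In the Analyses section, replace the independent-samples t test of gain with a linear model of AHA change that contains arm and House band (6-8 versus 4 or 5), for T1 minus T0 and for T2 minus T0. Report the adjusted difference between arms with its 95% confidence interval.

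Report a paired t test over the 12 pairs as a sensitivity analysis only. With 11 df its power falls to about 73.5% if gains are uncorrelated within pairs.

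The cost is one sentence of analysis wording and 1 degree of freedom, with no new data and no change to randomisation.

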### Sample size

According to CONSORT guidelines [31,32] the sample size estimates were based on projected treatment effect on the primary outcome measure, the Assisting Hand Assessment (AHA). The AHA scale's responsiveness to change has been shown in a study in which Eliasson et al [38] used the scale as the outcome measure in evaluating the effects of a modified model of CIMT. The authors reported a significant effect size of 1.16. Calculation by a statistician indicated that in order to detect a 1.16 effect size at significant level of 0.05 and 80% power a minimum sample size of 12 per group is required in our study.

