#### - Primary and secondary outcome measures

On the basis of our scientific hypothesis, the primary outcome measure of interest is bimanual UL activity performance using the AHA. Secondary measures include measure of unimanual capacity (Melbourne Assessment of Unilateral Upper Limb Function, MUUL) and the bimanual daily activities at home and in the community (ABILHAND-Kids). At the beginning of the study we intended to use also the Jebsen-Taylor Hand Function Test [42], but we realised that the test could be frustrating for some children with more severe impairment and, since the measure of dexterity was not an aim of our proposed rehabilitative approach we decided to skip this test from our measures.

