##### - Assisting Hand Assessment (AHA)

The primary outcome was the Assisting Hand Assessment (AHA, version 4.4) that is a standardised, performance-based test for use with children aged 18 months to 12 years, who have an unilateral upper limb impairment. It evaluates the spontaneous use of the assisting hand during a semi-structured 10-15 minutes play session with specific toys (from the AHA test kit) requiring bimanual handling [43,44]. The play context is age appropriate so there is one context for children 18 months to 5 years (Small kids AHA) and others (two different board games) for children aged 6-12 years (School Kids AHA). The forms are directly comparable as demonstrated by a test-retest of alternate forms of AHA [45]. The AHA is videotaped in a standardised manner and the subsequent scoring procedures produce a raw sum score ranging from 22 (low ability) to 88 (high ability) and a logit measure from -10.18 to +8.70. The AHA can only be administered and scored by a certified rater. Interrater, intrarater and test retest reliability of the AHA have a high ICC [45,46]. The Smallest Detectable Difference (SDD) over time indicated that a change in School Kids AHA scores from one test session to the next must be 3.65 sum scores (0.76 logits) or more to be considered a true change with 95% probability [45]. Also, the scale responsiveness to change was demonstrated in intervention studies focusing on forced use therapy [47], CIMT [38,44,46,48,49], HABIT [50] and, recently, modified CIMT followed by task-specific training of goal-directed bimanual play and self-care activities [51,52].

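### The AHA is compared between arms at both T1 and T2 at 0.05 with no primary visit named, although the sample size allows for a single test at 0.05

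*Protocol article*

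**What the plan says.** All references are to the protocol article.

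- **Primary outcome.** Under Primary and secondary outcome measures, "the primary outcome measure of interest is bimanual UL activity performance using the AHA". No visit is attached.
- **Visits.** Study design places assessments at baseline and "then on the week (T1) and 8 weeks (T2) after the end of the treatment". T1 and T2 are listed on equal terms. Only T3, at 24 weeks, has a separate role, which is retention.
- **Between-arm tests.** Analyses plans a t test for independent samples on the "differences between the follow-up assessment and baseline (T1 vs T0 and T2 vs T0"). The stated purpose is that it "will be performed for the comparison of the rehabilitative gain between the two groups".
- **Significance level.** The same section says "a significant level of 0.05 will be used", with no division between visits.
- **Sample size.** The calculation is based on the AHA and an effect size of 1.16 "at significant level of 0.05 and 80% power", which leads to 12 per group. Again no visit is named.

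**The concern.** The two t tests of change are the only between-arm tests of efficacy that the article specifies for the clinical outcomes. Applied to the AHA, they carry the primary claim. Each is run at the full 0.05, and nothing in the article's text says which one decides, whether both must succeed, or in what order they are read.

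A reader of the results could then accept a significant AHA difference at either visit as a positive trial. Under that rule, 0.05 is the error rate of each test but not of the claim, and the deciding visit could be chosen after the data are seen. This matters in a trial of 24 children that describes itself as the first test of this treatment in childhood.

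**Working it through.** **Inputs from the article.** Effect size 1.16, level 0.05, power 80%, 12 per group (Sample size); two between-arm t tests of change, T1 vs T0 and T2 vs T0, at 0.05 (Analyses).

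**Assumptions.** Tests are two-sided (sidedness is not stated). The same children contribute at both visits. The correlation r between the T1 and T2 changes is not in the article, so it is varied.

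**Step 1: reproduce the sample size.** With the two-sided normal formula for two means,

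n per group = 2 × (1.960 + 0.842)² / 1.16² = 2 × 7.849 / 1.3456 = 11.67, rounded up to 12.

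This matches the stated figure and supports the two-sided assumption; the one-sided version gives 10. An exact noncentral t calculation gives 13 per group, close enough not to change the reading. The planned size therefore corresponds to one test at the full 0.05.

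**Step 2: chance of at least one false positive.** With no treatment effect at either visit,

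P = 1 − P(|Z1| ≤ 1.96 and |Z2| ≤ 1.96),

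where Z1 and Z2 are standard normal with correlation r. At r = 0 this is 1 − 0.95² = 9.75%. The other normal-theory values are bivariate normal probabilities. The last column simulates two t tests with 12 per group (200,000 runs per value of r).

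| Assumed r | Normal theory | t-test simulation |
|---|---|---|
| 0 | 9.75% | 9.76% |
| 0.5 | 9.07% | 9.15% |
| 0.7 | 8.35% | 8.48% |
| 0.8 | 7.81% | 7.92% |
| 0.9 | 7.04% | 7.13% |
| 0.95 | 6.46% | 6.54% |
| 0.99 | 5.66% | not run |

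The figure approaches 5% only as r approaches 1. A range of 0.5 to 0.9 is plausible because both changes subtract the same T0 value and the article reports high reliability for the AHA, but it remains an assumption.

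**Step 3: compare remedies.**

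- *Fixed sequence (T1 at 0.05, then T2 at 0.05 only if T1 is significant).* If there is no effect at T1, any false claim requires a false rejection at T1, which has probability 5%. If there is an effect at T1 but none at T2, the only possible false claim is at T2, with probability at most 5%. The overall error is therefore at most 5%, and the T1 test keeps its full level and power.
- *Equal split (0.025 at each visit).* Simulated overall error is 4.7% at r = 0.5 and 3.7% at r = 0.9. The formula in Step 1 then needs 15 per group. Keeping 12 leaves about 67% power at each visit by noncentral t, against 77.5% at 0.05 by the same method.

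**The case against.** **No success rule is stated.** The article does not say that significance at either visit counts as success, and it describes p values as a measure of strength of evidence. This stands in part: the inflation is conditional on an either-visit rule. But the same sentence sets a 0.05 level, and no competing rule is given.

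**An order may be implied.** The aims ask first whether the method improves performance and then how long any effect lasts, which could suggest T1 before T2. This weakens a reading of the visits as deliberately co-equal. It does not make T1 primary, because the article links retention explicitly to T3 and puts both tests in one sentence.

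**A fuller document may settle it.** A full protocol or analysis plan could name the visit. That is possible, and if so the correction is only to carry it into the article. The point here rests on what the article does fix: two tests, one level, and a sample size built on one test.

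**Stronger readings that the article does not support.** A reader might infer any of the following:

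- *That the error rate simply is 7% to 9%.* It depends on an assumed correlation and on the either-visit rule.
- *That T3 adds a third primary test.* The between-arm tests in Analyses stop at T2.
- *That the two AHA scores double the tests.* The article describes a "raw sum score ranging from 22 (low ability) to 88 (high ability) and a logit measure from -10.18 to +8.70", but this explains how the instrument is scored. No separate test of each is planned.

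**Conclusion.** The point holds in a limited form. As written, the plan tests the primary outcome between arms twice at 0.05 without saying which visit carries the claim, while the sample size provides for one such test. If either visit counts as success, the overall two-sided error exceeds the nominal 5% unless the two changes are perfectly correlated. It is bounded by 5% and 9.75% for correlations from 1 down to 0, and is about 7% to 9% for an assumed correlation of 0.9 to 0.5. The missing primary visit is certain on the article's text; the exact size of the inflation is not. The flaw does not invalidate the trial, but it should be corrected.

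**What to change.** Before unblinding, name one primary comparison. One suitable wording: the primary analysis is the between-arm comparison of AHA change from T0 to T1 at two-sided 0.05; the change from T0 to T2 is tested at two-sided 0.05 only if the T1 comparison is significant, and is otherwise reported descriptively.

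This takes about a sentence, needs no more children and costs no power at T1. The downside is that an effect seen only at T2 becomes secondary evidence. Nothing in the article dictates T1: if the investigators regard the 8-week result as the main question, T2 can be named primary on the same terms. An alpha split would also control the error, but at the cost in sample size or power shown above.
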